### Patients’ selection, antibiotic regimen, and perioperative protocol

All patients undergoing radical or simple cystectomy (for all reasons) will be included. Inclusion and exclusion criteria are listed in Fig. 2. A urine culture will be performed 10 days before surgery and all patients will receive the same prophylactic antibiotic regimen: cefuroxime iv (single dose) and metronidazole IV (single dose) at the time of surgery for cystectomy with ileostomy/ureterocutaneostomy and cefuroxime iv and metronidazole IV (48 h after surgery) for cystectomy with orthotopic neobladder or heterotopic pouches. Patients will receive oral co-trimoxazole (single dose) at the time of ureteral stent removal. In case of allergies or antibiotic resistances according to the urinary culture, the antibiotic regimen will be adapted, and all changes will be recorded.

**Fig. 2 Fig2:**
[figure not shown]
Design of the study. INCyst Trial is a multicenter, prospective, controlled, pragmatic, single-blinded randomized controlled trial assessing the added value of preoperative immunonutrition (IN) on top of standard of care, as well as the clinical effect of IN on the onset of postoperative morbidity after cystectomy. CCI, Comprehensive Comorbidity Index; QoL, quality of life; ASS1, argininosuccinate synthetase 1. Created with BioRender.com

Each center will follow the same perioperative protocol according to the ERAS protocol for cystectomy [21]. The surgical procedure will be undertaken in a standardized technique among the three centers. As the robotic access is not routinely performed in Switzerland, only open cystectomies will be included. Bilateral PLND will be performed only in bladder cancer patients as an extended template. The mode of diversion/reconstruction will be left at the surgeon’s discretion but will be nevertheless documented. In case of orthotopic or heterotopic urinary diversion, the Studer technique will be performed.

A dedicated questionnaire (EORTC QLQ-C30) [22] will be distributed to patients assessing patients’ health status. The questionnaire will be discussed with each patient at visit V1 (inclusion), V5 (30 days after surgery), and V6 (90 days after surgery).

### Follow-up of adverse events (AE)

No AE related to the intake of immunonutrition are expected and therefore only 30-day and 90-day postoperative surgical complications will be reported to evaluate primary and secondary endpoints. All serious AEs will be followed until they are resolved or stabilized, including after the end of the study. If immediate safety and protective measures have to be taken during the conduct of the study, the investigator notifies the local ethics committee of these measures, and of the circumstances necessitating them, within 7 days.

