**Methods:**

This is a randomized, multicentric, controlled, pragmatic, parallel-group comparative study, supported by the Swiss National Science Foundation. A total of 232 patients is planned to be enrolled between April 2023 and June 2026. Three participating centers (Lausanne, Bern, and Riviera-Chablais) have been selected. All patients undergoing elective radical and simple cystectomy will be randomly assigned to receive 7 days of preoperative IN (Oral Impact^®^, Nestlé, Switzerland) versus standard of care (control group) and followed for 90 days after surgery. For the exploratory outcomes, blood, serum, urine, and stool samples will be collected in patients treated at Lausanne. In order to determine the impact of IN on immune fitness, patients enrolled at Lausanne will be vaccinated against influenza and the establishment of the vaccine-specific immune response will be followed. Analysis of the microbiota and expression of argininosuccinate synthetase 1 as potential biomarker will also be performed.

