**Laboratory samples (only Lausanne)**							
Blood (50ml/sample)	X	X				X	
Urine (5 to 300 ml/sample)	X	X				X	
Stools	X	X				X	
Arginine level	X	X					
Tissue (ASS1 expression analysis)		X					
Fresh Tissue (oncological patients)		X					
Influenza vaccination	X						
NRS	X						
Eligibility and Randomization	X						
Post-operative infectious complications						X	X
Comprehensive Complication Index (CCI)						X	X
EORTC-QLQ-C30 questionnaire	X					X	X
Peri-operative management					X		

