### Sample size calculations

The literature review showed a postoperative infectious rate between 25 and 45% among patients treated with cystectomy [4, 5]. Prior clinical data from cystectomy patients at CHUV resulted in an infectious rate at 30 days after surgery of 30%. As showed before, the literature review showed an infection between 25 and 45% among patients treated with cystectomy. Assuming a normal distribution for infectious complications after cystectomy and a common standard deviation in both study arms, desired probabilities of type I error (*α*) of 5% and of type II error (*β*) of 20% (i.e., 80% statistical power) and applying a two-sided test, 110 informative patients per arm (i.e., a total of 220) would be needed to decrease the rate of infectious complications by 17% in the IN group (37% infections at 30 days after surgery in the control group vs 20% in the IN group). Since we anticipate a possible dropout rate of up to 5%, a total of 232 patients are intended for enrolment in the study (116 patients per group). To achieve adequate participant enrolment, three Swiss hospitals participate to this study: University Hospital of Lausanne, University Hospital of Bern, and Hospital of Riviera-Chablais, with an estimated rate of recruitment of 50, 25, and 10 patients per year, respectively.

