### Statistical analysis

Ordinal and continuous data will be presented by study group in the form of descriptive statistics, as number of patients, mean, standard deviation, minimum, median, and maximum. Categorical data will be presented by study group using contingency tables with absolute and relative frequencies.

Complications rate will be presented using contingency tables with absolute and relative frequencies, overall and then by study group. The complication rate will be compared between groups using a Chi2 test. Mortality after surgery and postoperative complication-free survival will be analyzed using Kaplan–Meier curves. The study groups will be compared with a log-rank test. Nutritional status will be documented, and subgroup analysis of well-nourished patients randomized to the IN group will be undertaken at the end of the study. No imputations will be done on missing data. So, for longitudinal analysis mixed method analysis will be performed. Non-compliant patients from both arms will be maintained in the study, with no exclusion from the primary intention-to-treat analysis, however withdrawn from the per-protocol analysis. There is no data monitoring committee, owing to very good and well-known safety profiles of the IN and to the short follow-up period.

Other subgroup analyses will be performed (1) to test the effect of neoadjuvant chemotherapy and the risk of malnutrition on the primary outcomes and (2) to test the impact of the ERAS® compliance on the primary and secondary outcomes.

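### The adverse-event rule rests on immunonutrition alone and, as written, leaves out non-serious reactions to the influenza vaccine that the trial gives at Lausanne before surgery

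*Protocol article*

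**What the plan says.** The section on follow-up of adverse events gives one rule and one reason for it: "No AE related to the intake of immunonutrition are expected and therefore only 30-day and 90-day postoperative surgical complications will be reported". The sentence ends with a purpose clause: these complications "will be reported to evaluate primary and secondary endpoints". The next sentence is wider: "All serious AEs will be followed until they are resolved or stabilized, including after the end of the study". The section closes by requiring that immediate safety measures, and what made them necessary, be notified to the local ethics committee within 7 days.

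The supplement is not the only product that the trial gives. The Methods part of the Abstract says that "patients enrolled at Lausanne will be vaccinated against influenza and the establishment of the vaccine-specific immune response will be followed". The section on exploratory outcomes explains the purpose: influenza-specific T-cell responses are measured before and after vaccination to study the effect of immunonutrition on immunity. Table 2 has a row for "Influenza vaccination" with a single mark, at V0.

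Two other passages on safety also look to the supplement. The section on discontinuing or modifying interventions discusses only the safety record and side effects of immunonutrition. The statistical analysis section says: "There is no data monitoring committee, owing to very good and well-known safety profiles of the IN and to the short follow-up period".

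**The concern.** The rule is an inference: no reaction to the supplement is expected, therefore reporting can be confined to postoperative surgical complications. For patients at Lausanne the premise covers one of the two products they may receive. It says nothing about the vaccine, which is given for a research purpose shortly before major surgery and, as far as the article says, in both arms.

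What is at stake is safety information, not the treatment comparison. If sites follow the rule as written, the trial holds no systematic record of non-serious reactions to its own vaccination, nor of operations postponed by a reaction that does not meet the seriousness criteria. For serious reactions, the duty to follow them is stated, but the schedule shown does not say where before surgery anyone asks about them.

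**Working it through.** **1. Does the rule reach a vaccine reaction?** The relevant passages side by side:

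| Element | Place in the protocol article | Covers a vaccine reaction before surgery? |
|---|---|---|
| Reason for the restriction | Follow-up of adverse events | No: names immunonutrition intake only |
| Events reported | Same sentence | No: surgical complications at 30 and 90 days after surgery |
| Serious events | Next sentence | Yes, if serious: not limited by product or period, but the verb is *followed* |
| Immediate safety measures | Same section | Only if such a measure is taken |
| Discontinuing or modifying interventions | Section of that name | No: immunonutrition only |
| No data monitoring committee | Statistical analysis | No: safety profile of immunonutrition, and short follow-up |
| Collection of complications | Table 2 | No: infectious complications and the complication index at V5 and V6 only |
| Preoperative contact | Table 2, V1 | Physical examination and weight, but no event item |

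A non-serious reaction between V0 and surgery fails both conditions of the rule: it is not a surgical complication, and it is not postoperative. No other sentence picks it up.

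**2. Length of the window.** Table 2 puts V0 at day -30 to -8 and V1 at day -1 or 0.
- Shortest: from day -8 to day -1, 7 days.
- Longest: from day -30 to day 0, 30 days.

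**3. Number exposed.** The sample size section lists Lausanne, Bern and Riviera-Chablais "with an estimated rate of recruitment of 50, 25, and 10 patients per year, respectively". The target is 232.
- Share at Lausanne: 50 / (50 + 25 + 10) = 50/85 = 58.8%.
- Expected number: 232 × 50/85 = 136.5, taken as about 136.

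This assumes that sites recruit in proportion to the planned rates and that every Lausanne patient is vaccinated.

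The total of 232 itself reproduces. For 37% against 20%, two-sided 5% and 80% power, with pooled variance and no continuity correction:
- n per arm = [1.960 × √(2 × 0.285 × 0.715) + 0.842 × √(0.37 × 0.63 + 0.20 × 0.80)]² / 0.17² = 109.5, so 110.
- 220 / 0.95 = 231.6, so 232.

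Nothing in this point changes that calculation.

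**4. How many reactions might go unrecorded.** The article gives no reaction rate, so the rates below are assumptions. With N = 136, the expected count is N × p and the chance of at least one reaction is 1 − (1 − p)^136.

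| Assumed rate p | Expected count | Chance of at least one |
|---|---|---|
| 0.5% | 0.7 | 49% |
| 1% | 1.4 | 75% |
| 2% | 2.7 | 94% |
| 5% | 6.8 | 99.9% |

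**5. What recording would allow.** If a given type of reaction were asked about in all 136 patients and none occurred, the upper one-sided 95% limit for its rate would be 1 − 0.05^(1/136) = 2.2% (rule of three: 3/136 = 2.2%). If nobody asks, an absence of records supports no such limit.

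**The case against.** Four arguments stand against the point.

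**Serious events are covered.** A reader might infer that vaccine reactions are never reported, even serious ones. The article does not support that. Its sentence on serious events says all of them, without limit to product or period, and a serious reaction at Lausanne falls within it. The section on monitoring also has an independent monitor verify documentation and reporting against GCP and regulatory requirements. This argument stands for serious events. It does not reach non-serious ones, and following an event presupposes that someone detects it.

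**The restriction may concern endpoint data only.** The closing clause of the sentence ties the reporting to the primary and secondary endpoints, so it can be read as saying which events feed the endpoints rather than barring other safety records. That reading is fair. But the sentence stands in the section on adverse events, opens with an argument about which adverse events are expected, and is the only one that deals with non-serious events. At best the text is ambiguous, and a site could reasonably follow the narrower sense.

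**The article is condensed.** The route for reporting serious events, and detail on vaccine safety at one site, may sit in the full protocol. Their absence here is accordingly not the complaint. The complaint is that the article states a restrictive rule on a reason that omits one of the trial's own procedures.

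**The consequences are limited.** Vaccination is not tied to an arm, so the primary comparison is untouched. A reader might also infer that a patient lost because of a reaction would appear as an unexplained dropout. Nothing in the article says that reasons for dropout go unrecorded, so that is supposition. Nor would recording reactions show whether the vaccine caused harm: all Lausanne patients are to be vaccinated, so that site has no concurrent unvaccinated group. Both limits stand.

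**Conclusion.** The point holds within a narrow scope. The stated rule is justified by immunonutrition alone and, read as written, excludes non-serious reactions to the trial's own influenza vaccination, including one that postpones surgery without being serious. Serious reactions must be followed, but the schedule shown has no preoperative event collection to find them.

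The size is about 136 of 232 patients (59%), each with a window of 7 to 30 days. This rests on recruitment in proportion to the planned rates, on vaccination of all Lausanne patients, and on reading the single mark in Table 2 as V0. How many reactions would be missed cannot be derived from the article; section 4 of the working shows only a range under assumed rates.

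The sample size, the primary endpoint and the intention-to-treat comparison are not affected. This is a scope error in safety reporting that should be corrected. It does not threaten the trial's main conclusion.

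**What to change.** Reconcile the section on follow-up of adverse events with the Abstract, Table 2 and the section on exploratory outcomes, in three steps:

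1. Confine the word *only* to endpoint data, so that it defines which events enter the primary and secondary endpoints and no longer limits safety recording.
2. Add a sentence such as: *At Lausanne, adverse events after the study influenza vaccination are recorded from V0 to V1, with their seriousness and any postponement of surgery, and are reported descriptively, overall and by arm.*
3. Add the matching item to Table 2 at V1, an existing visit with a physical examination, and to the eCRF for Lausanne.

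The cost is one eCRF item and slightly more data entry at one site, with no extra visit. The report should say that these data describe reactions among vaccinated patients. The split by arm compares immunonutrition with control among vaccinated patients and does not estimate the effect of the vaccine.

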**Fig. 1 Fig1:**
[figure not shown]
Inclusion and exclusion criteria of the INCyst Trial

**Table 1 Tab1:** Trial registration data set according to World Health Organization

Data category	Information
Primary registry and trial identifying number	ClinicalTrials.gov NCT05726786
Date of registration in primary registry	March 9, 2023
Secondary identifying numbers	2022–01528 (Swissethics); SNCTP000005406 (KOFAM)
Source(s) of monetary or material support	Swiss National Science Foundation
Primary sponsor	University Hospital of Lausanne (CHUV)
Secondary sponsor(s)	None
Contact for public queries	[name]. [name] ([contact])
Contact for scientific queries	[name]. [name] ([contact])
Public title	The impact of immunonutrition on postoperative complications in patients undergoing bladder removal surgery
Scientific title	The role of preoperative immunonutrition on morbidity and immune response after cystectomy: protocol of a multicenter randomized controlled trial (INCyst Trial)
Countries of recruitment	Switzerland
Health condition(s) or problem(s) studied	Determination of infectious complications rate at 30 days after surgery
Intervention(s)	Drug: Oral Impact^®^, Nestlé Health Science, Switzerland
Key inclusion and exclusion criteria	Inclusion criteria: age ≥ 18 years, patient undergoing open cystectomy (for all reasons) Exclusion criteria: contraindications to immunonutrition (e.g., known hypersensitivity or allergy to lactose, fish oil, or soy lecithin), severe diarrhea requiring medical attention, current treatment with any immunosuppressive drug
Study type	Multicenter, prospective, controlled, pragmatic, parallel-group comparative study with block randomization stratified by centers
Date of first enrolment	April 2023
Target sample size	232
Recruitment status	Recruiting
Primary outcome(s)	Determination of the Comprehensive Complication Index (CCI) at 30 and 90 days after surgery Determination of the mortality rate at 30 and 90 days after surgery Determination of the postoperative complication-free survival
Key secondary outcome	Identification of biomarkers predictive of postoperative complications studying the patient’s immune and microbiome signature

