### Criteria for discontinuing or modifying interventions

Immunonutrition has been used for more than 15 years and no critical safety issues have been reported. Side effects (i.e., severe diarrhea or nausea requiring medical attention) related to the investigational product will not be considered as a criterion for discontinuation of the intervention.

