### Choice of comparators and protocol adherence

Oral Impact^®^ (IN) is an immune-modulating nutritional supplement containing arginine, omega-3 polyunsaturated fatty acids, and ribonucleic acid. Arginine is a key amino acid involved in multiple cellular processes as well as in lymphocyte function and its deficiency results in impaired adaptive immune response. It plays an active role in wound healing, muscle repair (by protein translation), and thrombosis prevention. The present design raises the issue of supplementing patients that are not at nutritional risk with Oral Impact®, resulting in overnutrition with potentially deleterious clinical consequences. However, this hypothesis has not been confirmed by others [23] and the product’s brochure stipulates that the administration of Oral Impact® in the preoperative phase is also indicated in well-nourished patients [24]. Moreover, surgery induces arginine deficiency and many patients with normal preoperative arginine concentrations cannot endogenously satisfy the metabolic demand after surgery.

Patients will be randomly assigned to receive 7 days of preoperative IN, three times a day (Oral Impact^®^) or will not receive oral IN supplements. Carbohydrate loading and protein drinks will be allowed in both groups. In the interventional group, patient’s compliance to the allocated treatment will be recorded by asking the patient how many nutritional supplements she/he has ingested preoperatively (ranging from 0 to 21 bags). Compliant patients will be defined by having drunk at least 14 of the 21 allocated nutritional supplements. To objectively verify and validate these subjective data, serum arginine levels will be assessed at enrolment (between day − 30 and day − 8) and at preoperative admission after intake of the allocated nutrition (day − 1).

Potential effective crossover between intervention groups will be assessed and recorded. As usual with interventions requiring voluntary adherence to a protocol, there is a risk for some participants from the IN arm do not comply with the intervention. Moreover, a mirroring risk exists for participants from the control group to access IN independently of the study protocol, since the product is commercially available. Recording such protocol deviations is mandatory for processing to a second line per-protocol analysis. However, the risks of crossover are very low.

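### The adverse-event section limits reporting because no intake-related event is expected, yet the next section names such events; the tolerability account of the 7 intake days is left unclear (minor)

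*Protocol article*

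**What the plan says.** The section Follow-up of adverse events (AE) gives a reason and a rule drawn from it: "No AE related to the intake of immunonutrition are expected and therefore only 30-day and 90-day postoperative surgical complications will be reported". The sentence ends with a purpose: "surgical complications will be reported to evaluate primary and secondary endpoints". The next sentence adds: "All serious AEs will be followed until they are resolved or stabilized".

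The section Criteria for discontinuing or modifying interventions says that the product has been in use for more than 15 years without critical safety issues. It then names "Side effects (i.e., severe diarrhea or nausea requiring medical attention) related to the investigational product" and says that these are not grounds for stopping the intervention.

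On exposure, Choice of comparators and protocol adherence says: "Patients will be randomly assigned to receive 7 days of preoperative IN, three times a day". Intake is recorded as the number of bags the patient reports, from 0 to 21, with serum arginine as a check. The same section sets the threshold: "Compliant patients will be defined by having drunk at least 14 of the 21 allocated nutritional supplements". Statistical analysis keeps non-compliant patients in the primary intention-to-treat analysis and removes them from the per-protocol analysis. Clinical outcomes lists treatment compliance among the further outcomes.

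**The concern.** The reporting limit rests on the expectation that the product causes no adverse events. The section that follows sets a rule for adverse events caused by the product. If that rule is needed, the expectation is a weak reason for not reporting them.

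The limit also falls in an awkward place. Exposure ends at surgery and the reported windows begin at surgery. A non-serious episode of diarrhea or nausea caused by the product would most likely occur during intake, where the rule as written has no place for it.

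Two things are at stake. The first is a plain account of how well the product was tolerated, which a clinician would want beside any benefit. The second is the meaning of the compliance result and the per-protocol set. A patient who stops drinking because of the product can leave that set, and the report might not show why.

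**Working it through.** The plan gives no figure on this point, so the check is mainly a comparison of statements.

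**1. Premise against the next section.** The adverse-event section expects no intake-related event. The discontinuation section names two kinds, both severe enough to need medical attention, and calls them related to the product. It gives no frequency and does not say that they are expected. The two statements can both be true if the events are thought possible but rare. Even so, a recognised possible side effect undercuts the inference from none expected to none reported.

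**2. Exposure against the reporting window.** Intake covers the 7 days before surgery. The reported windows run to 30 and 90 days after surgery. They do not overlap.

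**3. Other routes in Table 2.** The schedule has no row for adverse events or tolerance.
- V1 (day -1/0), straight after intake, lists a physical examination and weight.
- Infectious complications and the complication index appear only at V5 and V6.
- The quality-of-life questionnaire is marked at V0, V5 and V6.

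Patients are therefore seen at the right moment, but the article does not say that they are asked about tolerance.

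**4. Which reading of the sentence?**
- Broad reading: only postoperative complications are reported at all. The stated reason is about intake events, which would be irrelevant if the sentence merely listed endpoint data. The words *therefore only* also point this way.
- Narrow reading: the sentence defines the data used for the endpoints. Its closing clause supports this, and the endpoints that it serves are postoperative.

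The broad reading is the more natural, but the wording does not exclude the narrow one. On both, serious events are followed, so the possible gap concerns non-serious events only.

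**5. Link to planned analyses.** A patient needs at least 14 of 21 bags to be compliant, so 21 - 13 = 8 missed bags is enough to leave the per-protocol set. The bag count and the arginine check show how much was taken. Neither shows why bags were missed.

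**6. What is untouched.** The sample size uses only the infection rates of 37% and 20%. With a pooled-variance two-sided test at 5% and 80% power:

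n = [1.960 × √(2 × 0.285 × 0.715) + 0.842 × √(0.37 × 0.63 + 0.20 × 0.80)]² / 0.17² = 109.5, rounded up to 110 per arm.

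220 / 0.95 = 231.6, rounded up to 232. Both match the article, and neither depends on adverse-event data.

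**7. Scale, by assumption only.** The article gives no rate for these side effects. If 1% to 10% of the 116 patients in the immunonutrition arm had one, that would be 116 × 0.01 = 1.2 to 116 × 0.10 = 11.6 patients. Any serious cases among them would be followed, so the number possibly unreported is at most this.

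**The case against.** The strongest defence is the closing clause of the sentence: it concerns endpoint data, and limiting endpoint data to postoperative complications is natural. This stands as a possible reading. It does not explain why the sentence opens with a reason about intake events.

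Second, a reduced adverse-event scope is defensible for an oral supplement with long use and no reported critical safety issues. This also stands. The point is not that full adverse-event collection is required, but that the reason given does not fit the next section.

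Third, tolerability questions and reasons for missed bags are case-report-form content, which an article leaves to the full protocol. Their absence from the article is indeed no finding in itself. What remains is the restriction that the article does state, and the reason that it gives.

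A reader might infer more than the documents support:
- **That intake-period events will certainly go unreported, or that safety is not followed.** The narrow reading is open, serious events are followed, and some of the named events could qualify as serious.
- **That the exclusion criteria confirm the problem.** Table 1 excludes patients with "severe diarrhea requiring medical attention, current treatment with any immunosuppressive drug". That screens patients before entry and does not say that the product causes diarrhea.
- **That the main result is biased.** Non-compliant patients stay in the primary analysis. The per-protocol analysis is described as second line, and compliance is itself an outcome, so its extent will be visible. Only its cause might be missing.

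**Conclusion.** The point holds in a limited form. The stated reason for restricting reporting is undercut by the section that follows it. On the more natural reading, non-serious events in the 7 preoperative intake days are not reported. The narrower reading is possible, and the article does not settle the matter.

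Severity is minor. The consequence is confined to the tolerability account and to the interpretation of compliance and the per-protocol set. The primary endpoint, the sample size and the intention-to-treat analysis are unaffected. The number of patients concerned cannot be derived from the article.

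The conclusion rests on the article's wording alone. If the full protocol's forms already collect tolerability and reasons for missed intake, what remains is a sentence to correct.

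**What to change.** 1. In Follow-up of adverse events (AE), delete the opening premise and the words *therefore only*, so that the sentence simply defines the postoperative data used for the endpoints. Leave the sentence on serious events as it is.
2. At V1, ask patients in both arms whether they have had a gastrointestinal event requiring medical attention since randomization. Tabulate the answers by arm descriptively, without a test.
3. In the immunonutrition arm, record the main reason for missed bags (gastrointestinal or other) beside the existing bag count.

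If the full protocol's forms already hold items 2 and 3, only item 1 is needed.

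The cost is low: a wording change and one short eCRF item, with the reason field, at a visit that already takes place. The section Protocol amendments requires ethics approval before substantial changes, so an amendment may be needed. Table 1 gives the status as recruiting, so the new data would come only from patients who reach V1 after the change. The table should state that date and the number of patients per arm. The control arm takes no product and patients know what they received, so the comparison can only be descriptive.
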